**Primary objective**

1. To identify the incidence and severity of nasal injury at removal of CPAP in all the three groups (i.e. rotation group, mask continue group, prong continue group) based on the objective scoring and a subjective assessment.

**Secondary objectives**

To compare the following among the groups (prongs vs. masks vs. rotation of mask and prongs)

- The need for mechanical ventilation.
- The duration of CPAP, oxygen and ventilation
- Incidence of bronchopulmonary dysplasia as defined by requirement of oxygen or any form of respiratory support till 28 days of life (BPD)
- Ventilator associated pneumonia (VAP) as per NEO-KISS criteria
- Intraventricular haemorrhages (IVH) as defined by Papille et al.
- Periventricular leucomalacia (PVL) at discharge according to de Vries criteria
- Mortality among the groups will be noted till the baby is in NICU

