A study conducted by Avery et al in 1987 comparing the outcome in eight different academic centers in USA noted that the best survival without BPD was noted in institutions that used nasal CPAP extensively for the stabilization of very low birth weight (VLBW) babies.^(12)^ Schmölzer performed a meta-analysis and included 4 trials (COIN, SUPPORT, CURPAP and VON) with a total of 2780 preterm infants (<32 weeks GA). The pooled results for the combined outcome death or BPD showed a reduction in favour of delivery room NCPAP compared to intubation with a relative risk 0.90 (0.83-0.98 95% CI) and numbers needed to treat (NNT) of 25^(13)^. Currently nasal continuous positive airway pressure (NCPAP) is the most commonly used respiratory support for newborn infants. It is a technique for non-invasive respiratory support of both term and preterm infants with respiratory distress.

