Emily A. Kieran et al 2012^(16)^ compared nasal mask vs nasal prong as an interface to deliver nCPAP with need for ventilation as primary outcome and nasal injury as secondary outcome.120 infants were enrolled. Thirty-two of 62 (52%) infants randomly assigned to prongs were intubated within 72 hours, compared with 16/58 (28%) of those randomly assigned to mask (P = .007). Nasal injury occurred in 2 infants in each group with no statistically significant difference. Authors concluded that in premature infants, NCPAP was more effective at preventing intubation and ventilation within 72 hours of starting therapy when given via nasal masks compared with nasal prongs with no increased risk of nasal injury.

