**OUTCOMES MEASURED**

Six hours after the removal of nCPAP, infants will be assessed for nasal injury (Table 1) and digital photographs will be taken that will be reviewed by a senior neonatologist blinded to the study group allocation. Incidence and severity of nasal injury is the primary outcome of the study. Bedside subjective assessment of nasal injury will also be done by one of research assistant and this included; a) dilation of nares, b) columella indentation or excoriation, c) notching on the bridge of nose, d) altered shape of nose and e) redness /indentation/bleeding/excoriation of any area of nose.

The secondary outcomes of the study includes nCPAP failure, duration of nCPAP, duration of oxygen, culture positive sepsis, BPD, Intraventricular haemorrhages (IVH) grade ≥ 3. cystic periventricular leukomalacia (PVL), retinopathy of prematurity and mortality. Data will be collected until death or discharge from the hospital.

**Figure 1:** Clinical trial protocol for titration, weaning and removal of CPAP

[figure not shown]

Note: Titration will be done primarily based on clinical features and pulse oxygen saturation; arterial blood gas and chest X ray will be used for decision making wherever available

* <6 and >8 posterior intercostals spaces is defined as under and over inflation respectively, ^£^ICR: Intercostal Retractions

**Weaning of CPAP**: Weaning from CPAP will be attempted if the infant will have good respiratory efforts and will be free of apneas and bradycardia in the past 24 hours and if one or more of the following will be present:

1. Stable or decreasing oxygen requirement over the past 12 hours
2. Chest wall hyperinflated* (either clinically or in a Chest X ray) with absence of retractions and a pulmonary air leak ruled out.

Note: If the infant did not tolerate the decrease in CPAP, as judged by an increase in oxygen requirement by 15% more than that in the preceding 12 hours, the CPAP pressure will be again increased by1 cm of H_2_O.

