| S.No | Items | | Response | | | | | | | | | | | | | | |
| 1 | Blood culture proven Sepsis | | Y / N Organism_______________ | | | | | | | | | | | | | | |
| 2 | Duration of Antibiotics | | __________________________days | | | | | | | | | | | | | | |
| 3 | Respiratory distress syndrome | | Y / N | | | | | | | | | | | | | | |
| 4 | Study start age (hours) | |  | | | | | | | | | | | | | | |
| 5 | Surfactant | | Y / N | | | | | | | | | | | | | | |
| 6 | Age of giving surfactant (hours) | |  | | | | | | | | | | | | | | |
| 7 | Second dose of surfactant | | Y / N | | | | | | | | | | | | | | |
| 8 | SAS score at time of randomization | |  | | | | | | | | | | | | | | |
| 9 | FiO2 at start of intervention | |  | | | | | | | | | | | | | | |
| 10 | Maximum FiO2 required | |  | | | | | | | | | | | | | | |
| 11 | Flow at start of study | |  | | | | | | | | | | | | | | |
| 12 | Initial choice of interface | |  | | | | | | | | | | | | | | |
| 13 | Age at change of first choice interface (hours) | |  | | | | | | | | | | | | | | |
| 14 | Duration of CPAP ( hours) | |  | | | | | | | | | | | | | | |
| 15 | Duration of Mask as interface ( hours) | |  | | | | | | | | | | | | | | |
| 16 | Duration of Prongs as interface ( hours) | |  | | | | | | | | | | | | | | |
| 17 | Duration of oxygen all forms ( days) | |  | | | | | | | | | | | | | | |
| 18 | Any adverse event during CPAP | | Y / N | | | | | | | | | | | | | | |
| 19 | Maximum nasal injury score | |  | | | | | | | | | | | | | | |
| 20 | Nasal injury score at discharge | |  | | | | | | | | | | | | | | |
| 21 | Pneumonia | |  | | | | | | | | | | | | | | |
| 22 | NEC | | Y / N Stage: _______ | | | | | | | | | | | | | | |
| 23 | PDA | | Y / N Medical / surgical | | | | | | | | | | | | | | |
| 24 | IVH ( grade 3 or 4) | | Y / N Grading________ | | | | | | | | | | | | | | |
| 25 | Cystic PVL (Grade≥2) | | Y / N Grading________ | | | | | | | | | | | | | | |
| 26 | ROP | | Y / N Grading________ | | | | | | | | | | | | | | |
| 27 | ROP requiring laser | | Y / N | | | | | | | | | | | | | | |
| 28 | Supplemental oxygen at 28 days of life, | | Y / N | | | | | | | | | | | | | | |
| 29 | BPD (use of supplemental oxygen at 36 weeks postmenstrual age) | | Y / N | | | | | | | | | | | | | | |
| 30 | Pulmonary air leaks (pneumothorax, PIE) | | Y / N | | | | | | | | | | | | | | |
| 31 | Neonatal mortality | | Y / N | | | | | | | | | | | | | | |
| 32 | Age at discharge (day of life) | |  | | | | | | | | | | | | | | |

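### Early death precludes BPD and shortens the support durations, and CPAP failure shortens CPAP duration, so these secondary outcomes compared raw can favour the arm that did worse

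*Protocol*

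**What the plan says.** The Secondary objectives of the protocol include "Incidence of bronchopulmonary dysplasia as defined by requirement of oxygen or any form of respiratory support till 28 days of life (BPD" and "The duration of CPAP, oxygen and ventilation". The section on outcomes measured repeats most of this: "The secondary outcomes of the study includes nCPAP failure, duration of nCPAP, duration of oxygen, culture positive sepsis, BPD", with mortality as a further separate item.

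The Enrolment Form in Annexure 1 records "Duration of CPAP ( hours" and "Duration of oxygen all forms ( days" as single totals. It also carries a second BPD definition, "BPD (use of supplemental oxygen at 36 weeks postmenstrual age", answered yes or no with no option for an infant who died before that age. Neonatal mortality is likewise yes or no. The form shows no field for age at death, time of intubation or duration of ventilation.

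The Statistical analysis section names intention to treat, chi-square or Fisher's exact tests, ANOVA and Mann-Whitney. It gives no composite outcome and no method for events that cut an outcome short. The literature review does cite a composite: "The pooled results for the combined outcome death or BPD showed a reduction in favour of delivery room NCPAP compared to intubation".

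**The concern.** BPD under either definition can be diagnosed only in an infant who lives long enough. A duration total ends when support ends, and it does not distinguish successful weaning from intubation or death. Infants in this trial are at or below 30 weeks, with a stratum below 28 weeks, so deaths cannot be assumed away.

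The two events act on different outcomes:

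- **Early death** prevents a BPD diagnosis and shortens the CPAP, oxygen and ventilation totals.
- **CPAP failure** shortens the CPAP total only. A ventilated survivor still accrues oxygen time and still counts as on respiratory support for BPD.

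If either event is more frequent in one arm, the affected outcome is pulled in that arm's favour. A shorter CPAP course or a lower BPD rate could then reflect more failures or more deaths rather than better respiratory recovery.

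**Working it through.** The protocol gives no figure for this point. Its 48 and 55 per group concern nasal injury and play no part here. The checks below show direction and rough size under stated assumptions.

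**1. Death and BPD.** Let b be the BPD risk among survivors, equal in both arms, and d the proportion who die before BPD can be diagnosed. Keeping all randomised infants in the denominator:

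- BPD = b(1 − d)
- death or BPD = d + b(1 − d)

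With b = 40% and d = 15% vs 5% (all assumed):

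| | d = 15% | d = 5% |
|---|---|---|
| BPD | 0.40 × 0.85 = 34% | 0.40 × 0.95 = 38% |
| Death or BPD | 15 + 34 = 49% | 5 + 38 = 43% |

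The order reverses. In general the higher-mortality arm gains b × (difference in d) on BPD and loses (1 − b) × (difference in d) on the composite. For b from 20% to 50% and deaths of 15% vs 5%, 20% vs 10% or 30% vs 10%, the gain is 2 to 10 points and the loss 5 to 16 points.

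**2. Death and oxygen duration.** Assume survivors need 10 days and deaths occur on day 3. Deaths of 20% give 0.8 × 10 + 0.2 × 3 = 8.6 days on average. Deaths of 10% give 0.9 × 10 + 0.1 × 3 = 9.3 days. The arm with more deaths looks better.

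**3. CPAP failure and CPAP duration.** Two mask-versus-prong trials in the protocol's Nasal Interface section supply failure rates. The 120-infant trial reports "Thirty-two of 62 (52%) infants randomly assigned to prongs were intubated within 72 hours, compared with 16/58 (28"%). The 118-infant trial reports failure in 25% on prongs and 13% on mask, not statistically significant.

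Assume that failures are uniform over 0 to 3 days, that CPAP time stops at failure, and that successes last 3 days plus an exponential time, with median m among successes. For failure proportion f, the arm's median is:

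- 3 × 0.5/f when f is above 50%
- 3 + (m − 3) × log2[2(1 − f)] when f is below 50%

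With m = 7 days:

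| Failure | Calculation | Median |
|---|---|---|
| 52% | 3 × 0.5/0.52 | 2.88 d |
| 28% | 3 + 4 × log2(1.44) = 3 + 4 × 0.526 | 5.10 d |
| 25% | 3 + 4 × log2(1.50) = 3 + 4 × 0.585 | 5.34 d |
| 13% | 3 + 4 × log2(1.74) = 3 + 4 × 0.799 | 6.20 d |

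The higher-failure arm looks shorter by about 2.2 days at 52% vs 28%, and by about 0.9 day at 25% vs 13%. For m from 4 to 10 days the gaps run from 0.6 to 3.8 days and from 0.2 to 1.5 days.

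**4. CPAP failure and oxygen duration.** Assume 7 oxygen days without intubation, 14 with it, and no deaths. Failure of 13% gives 0.87 × 7 + 0.13 × 14 = 7.9 days. Failure of 25% gives 0.75 × 7 + 0.25 × 14 = 8.8 days. Here the arm with more failures looks worse, as it should.

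**The case against.** A reader might infer that more intubations make an arm look better on all these outcomes. The documents do not support that. The BPD objective counts any respiratory support and the form counts oxygen in all forms, so step 4 runs the other way.

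A reader might also infer that the protocol scores a death as free of BPD. It does not say so. That scoring follows only if intention to treat keeps every randomised infant in the denominator. Nor does it say that a shorter duration is better. Denominators may be settled in an analysis plan that is not shown. This objection stands in part, but the alternative of analysing survivors only conditions on an event after randomisation and so does not remove the difficulty. The choice of outcome, and what the form collects, belong to the protocol.

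Mortality, nCPAP failure and need for ventilation are separate outcomes, so an imbalance would be visible beside BPD and the durations. This weakens any claim that the trial would present harm as benefit. It does not correct the affected outcomes themselves.

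The failure contrasts are prongs against mask, and the protocol's own reading of the literature is that the two are equally effective. No cited figure shows that rotation changes failure. The second randomisation also takes only infants still on CPAP after 8 hours. Under the uniform assumption, 8/72 = one-ninth of failures precede it. CPAP resumed after extubation would add hours and narrow the gap. These points bear on size more than on direction.

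**Conclusion.** The point holds in limited form. Early death precludes BPD and shortens all three durations; CPAP failure shortens CPAP duration only. Raw comparison of all randomised infants can therefore favour an arm with more deaths, or, for CPAP duration, more failures.

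The size depends on between-arm differences that the protocol does not give. The death rates, survivor BPD risk and timing of failure above are assumptions. In the BPD illustration the 4-point difference is about two infants in an arm of 55 (0.04 × 55 = 2.2), so what matters is the reversed direction rather than a large false effect. A reader should not extend this to nasal injury or the sample size: only secondary outcomes are involved.

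**What to change.** - **BPD.** First reconcile the day-28 definition in the Secondary objectives with the 36-week definition on the Enrolment Form. Then report death or BPD at the agreed time point, with BPD among survivors and mortality beside it.
- **Durations.** Replace raw totals with days alive and free of CPAP, of oxygen and of ventilation to day 28. Score death as 0 days and do not count ventilator days as free. State the convention for infants discharged before day 28, since data collection ends at discharge. Alternatively, for CPAP, analyse time to successful removal under the protocol's own removal criteria, with intubation and death as competing events.
- **Form.** Add age at death and the start and stop dates of each type of support.

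The cost is outcome wording, a modest amount of analysis and a few dates from the hospital record. No extra infants or visits are needed. The composite does mix death with a less severe outcome, which is why its components should be shown with it.

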**MATERIAL & METHODS**

Study site:

NICU, Fernandez Hospital, Hyderabad.

Study design:

A Prospective, Randomized, Comparative study.

Sample size with justification:

Assuming an incidence of nasal injury of 50% among the control group at the removal of CPAP from literature review and previous study from our center^(2-6)^. Assuming three group comparisons with an effect size of 30% with 80% power, alpha error of 5% the sample size calculated is 48 in each group and assuming an attrition rate of 10% we need 55 neonates in each group. Sample size was estimated by using Compare k Proportions: 1- way ANOVA Pairwise test ([www.powerandsamplesize.com](http://www.powerandsamplesize.com)). We will enroll patients till a minimum of 55 infants are enrolled in each group.

Time frame:

From september 2016 to march 2018.

Study population

Neonates admitted in NICU for respiratory distress

Inclusion criteria

- All inborn neonates <=30 weeks of gestation and
- Developed respiratory distress (presence of at least two out of three signs: tachypnea > 60/min, intercostal retractions, and expiratory grunt) within 6 hours of life.

Exclusion criteria

- Patients who have Perinatal depression (5 minute Apgar score of ≤3),
- Patients with Life threatening congenital malformations such as congenital diaphragmatic hernia, and trachea-esophageal fistula, other malformations that would prevent from establishing CPAP due to the anatomical defect such as Pierre-Robinson syndrome and choanal atresia
- Conditions where CPAP would be contraindicated such as neonates with poor spontaneous respiratory efforts or apnea, worsening shock, suspected or proven persistent pulmonary hypertension of newborn, severe metabolic acidosis (pH<7.2 with base deficit > -10), severe respiratory acidosis (pH<7.2 with PaCO2>55mmHg) and massive pulmonary hemorrhage

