| 1 | Abnormalities of upper and lower airways precluding use of CPAP or HHHFNC (Pierre-Robin, Treacher Collins, Goldenhar, choanal atresia, cleft lip/palate) | | Y / N | | | | | | | | | | | | | | | | | | | | | | | | | |
| 2 | Serious abdominal, cardiac, or respiratory malformations including tracheal esophageal fistula, intestinal atresia, omphalocele, gastrochisis, or diaphragmatic hernia | | Y / N | | | | | | | | | | | | | | | | | | | | | | | | | |
| 3 | Required intubation at birth | | Y/N | | | | | | | | | | | | | | | | | | | | | | | | | |
| 4 | Perinatal depression (5 minute Apgar score of ≤3) | | Y/N | | | | | | | | | | | | | | | | | | | | | | | | | |
| **Consent**  ***(If response to all the exclusion criteria is No, obtain consent from parent/ attendant)*** | | | | | | | | | | | | | | | | | | | | | | | | | | | | |
| S.No | Items | | Response | | | | | | | | | | | | | | | | | | | | | | | | | |
| 1 | Written and verbal consent obtained from parent/ direct care taker of the baby? | | Y / N | | | | | | | | | | | | | | | | | | | | | | | | | |
| 2 | If ‘Y’, have you enrolled the baby? | | Y / N | | | | | | | | | | | | | | | | | | | | | | | | | |

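### The metabolic-acidosis exclusion pairs base deficit with a negative limit, so neither its literal reading nor its base-excess reading matches its own label

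*Protocol*

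**What the plan says.** In the protocol's Material & Methods, the third exclusion bullet opens with "Conditions where CPAP would be contraindicated such as neonates with poor spontaneous respiratory efforts or apnea, worsening shock" and goes on to two acidosis conditions, one metabolic and one respiratory: "severe metabolic acidosis (pH<7.2 with base deficit > -10), severe respiratory acidosis (pH<7.2 with PaCO2>55mmHg". The base-deficit limit has no unit.

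This bullet is the only place where the rule appears. The Screening Form in Annexure 1 has four exclusion items: airway abnormalities, serious malformations, intubation at birth and, last, "Perinatal depression (5 minute Apgar score of ≤3) | | Y/N". None of them asks for pH, base deficit or PaCO2. The form moves on to consent when all four are answered No.

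**The concern.** Base deficit is base excess with the sign reversed, and it is positive in metabolic acidosis. A negative limit with a greater-than sign therefore does not describe a severe deficit. The two direct ways of applying the printed rule lead to different populations, and neither is the one that the label names.

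What is at stake is eligibility and its reproducibility. Two investigators in the unit could classify the same blood gas in opposite ways, each with some support from the text, and a later check of eligibility would have no clear standard. The bullet is also meant to keep out infants in whom the protocol considers CPAP contraindicated, so the direction of the inequality matters.

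**Working it through.** The plan gives no figure to reproduce here. The check has a logical part, which needs only the sign identity, and an illustrative part, which needs an outside formula.

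**Inputs from the protocol (Exclusion criteria).** Metabolic limb: pH < 7.2 and base deficit > -10. Respiratory limb: pH < 7.2 and PaCO2 > 55 mmHg.

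**Step 1: sign identity.** Base deficit (BD) = -base excess (BE), so BD > -10 is the same as BE < +10. For an infant with pH < 7.2, the table shows whether the metabolic limb is met under each reading:

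| BE | BD | Literal: BD > -10 | As base excess: BE > -10 | By magnitude: BD > 10 |
|---|---|---|---|---|
| -20 | 20 | yes | no | yes |
| -15 | 15 | yes | no | yes |
| -11 | 11 | yes | no | yes |
| -8 | 8 | yes | yes | no |
| -5 | 5 | yes | yes | no |
| 0 | 0 | yes | yes | no |
| +9 | -9 | yes | yes | no |
| +10 | -10 | no | yes | no |

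The literal clause is met even at BE 0, where there is no metabolic acidosis. The base-excess reading selects in the wrong direction. Only the last column selects the more severe cases.

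**Step 2: what the literal clause does to the respiratory limb.** This step assumes a simplified Van Slyke relation with Henderson-Hasselbalch, neither of which is in the protocol:

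- HCO3 = 0.0307 × PaCO2 × 10^(pH - 6.1)
- BE = 0.93 × (HCO3 - 24.4 + 14.83 × (pH - 7.4))

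To escape the literal metabolic limb, an infant needs BE of at least +10. At pH 7.19 that means HCO3 = 10/0.93 + 24.4 + 14.83 × 0.21 = 38.3, and PaCO2 = 38.3 / (0.0307 × 10^1.09) = about 101 mmHg. At pH 7.10 it is about 129 mmHg. Such infants already exceed 55 mmHg. The two limbs together therefore amount to pH < 7.2 alone, and the PaCO2 limit is redundant in practice.

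**Step 3: who is excluded only because of the literal text.** Take as comparator a magnitude of 10 in the acidotic direction together with the printed PaCO2 limit. The affected infants have pH < 7.2, BD of 10 or less, and PaCO2 of 55 or less. The PaCO2 at which BD equals 10 is:

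| pH | PaCO2 at BD 10 (mmHg) | Affected PaCO2 range (mmHg) |
|---|---|---|
| 7.19 | 44.4 | about 44 to 55 |
| 7.15 | 50.4 | about 50 to 55 |
| 7.13 | 53.7 | about 54 to 55 |
| 7.12 | 55.4 | none |
| 7.10 | 58.9 | none |

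Example: pH 7.19 with PaCO2 50 gives HCO3 18.9 and BE -8.0. The printed text excludes this infant under both the literal and the base-excess reading, although BD is below 10 and PaCO2 is below 55. The affected group is a wedge that closes at about pH 7.12. Using 14.8 in place of 14.83 moves these boundaries by less than 0.1 mmHg; a different base-excess formula could move them more.

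**Step 4: who the base-excess reading misses.** pH 7.10 with PaCO2 40 gives HCO3 12.3 and BE -15.4. Since -15.4 > -10 is false and 40 > 55 is false, neither acidosis limb catches this infant by its numbers. The same holds at pH 7.00 with BE -20, where PaCO2 is about 36.

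**The case against.** The strongest reply is that the label settles the meaning. The limit stands in brackets after the words for severe metabolic acidosis, in a bullet about contraindications to CPAP, and only a reading by magnitude fits. Staff in a neonatal unit may well read it that way, in which case the slip has no consequence. This stands as a reason to expect limited harm. It does not make the printed text correct, and no other section of the protocol confirms that reading.

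Several stronger inferences are tempting and should be resisted:

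- **A safety problem with severe cases randomised.** The bullet's list is introduced as examples, and an infant with BE -15 still has the named condition. Such an infant may also be excluded for shock, apnoea or poor respiratory effort. Step 4 shows only that the numerical limits miss the infant, not that enrolment would follow.
- **More early CPAP failures.** No figure in the protocol supports this. Moreover, the second randomisation, which allocates rotation, takes in only infants still on CPAP after 8 hours.
- **Different rules at different sites.** The protocol names one NICU. Inconsistency between investigators within it is possible, but nothing in the document shows it.
- **Wholesale loss of infants with pH below 7.2.** The literal text does exclude practically all of them. Most of that region, however, would also be excluded by a magnitude limit of 10 or by the PaCO2 limb; step 3 shows that the difference is a small wedge.

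It is also fair to say that the criterion may hardly operate, because the screening form does not collect it. That is a reason to add the item, and it leaves the actual effect unknown.

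**Conclusion.** The criterion is wrong as written: term, sign and direction do not agree with each other or with the label. The conclusion rests on the sign identity alone. The wedge between about pH 7.12 and 7.20 with PaCO2 at or below 55 mmHg rests on an assumed formula and on 10 being the intended magnitude; it is an illustration of size, not an estimate.

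The number of infants affected cannot be derived, because the protocol does not say how many have pH below 7.2 at entry. A reader might infer bias or lost power, but the documents do not support that. Eligibility is applied before allocation and equally to all groups. The sample-size calculation uses the control incidence, the effect size, power, alpha and attrition, none of which depends on this criterion. This is a notation error in an eligibility rule that merits correction, and no more than that.

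**What to change.** The sponsor should reconcile the metabolic-acidosis line under Exclusion criteria so that the limit agrees with its label. Two forms would be consistent: base deficit with a positive limit and greater than, or base excess with a negative limit and less than. The unit should be stated, and the sponsor should confirm the intended limit; which value is clinically right is not judged here.

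The same line should then be added to the exclusion items of the Screening Form, which has no acidosis item at present, so that its application is recorded. The cost is one corrected line in the protocol and one added line on the form. The correction itself asks for no test beyond those that the printed criterion already needs, and for no more patients.
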